**Figure 1 F1:**
[figure not shown]
Study algorithm. eGFR, estimated glomerular filtration rate; Hx, History of …; LDL-C, low-density lipoprotein-cholesterol; NSTEMI, Non-ST-segment myocardial infarction; STEMI, ST-segment myocardial infarction.

Group A will consist of the subgroup of patients who do not reach the LDL-C guideline target [LDL-C < 1.4 mmol/L (55 mg/dL)] after 6 weeks and will receive additive bempedoic acid (180 mg/day) for another 8 weeks (Triple therapy). Group B will consist of the subgroup of patients who achieve the LDL-C guideline target after 6 weeks of treatment with atorvastatin plus ezetimibe and who will continue on dual therapy for another 8 weeks (Dual therapy).

The 6-week escalation interval reflects local healthcare system, including certain reimbursement constraints, while aligning with evidence-based preferences to minimize delays in treatment intensification.

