We planned and initiated the HAnnover ChOlesterol Lowering in Acute Coronary Syndrome (HACOL-ACS) trial to address three major clinically relevant questions: First, how many patients after a myocardial infarction reach the guideline-recommended target [LDL-C < 1.4 mmol/L (55 mg/dL)] on dual therapy with atorvastatin (at least 40 mg/day or equivalent) plus ezetimibe (10 mg/day)? Second, how many of the patients not achieving the target on a dual statin/ezetimibe therapy reach the target after adding bempedoic acid? Third, how many patients miss the target despite escalated oral triple lipid-lowering therapy and therefore need referral for PCSK9 inhibition? Our trial is distinct from the ES-BempedACS trial, as it focuses exclusively on patients without previous lipid-lowering therapy and will demonstrate the exact additive impact of bempedoic acid on top of dual therapy in each patient due to its sequential escalation strategy. Thereby, we will evaluate the real-world, guideline-mandated stepwise oral escalation therapy and quantify the residual unmet need for LDL-C target achievement. Starting with dual background medication is consistent with current guideline recommendations (17), and sequential add-on with bempedoic acid is also guideline-recommended (17), although this approach has never been tested in clinical practice. It is therefore important to document the efficacy of additive bempedoic acid on top of established and tolerated high-intensity statin treatment in combination with ezetimibe, to provide data supporting such recommendations. This is particularly important for the trial to be conducted in a sequential and clear manner as recent data from the ES-BempedACS trial with varying pretreatment populations did not show an additive LDL-C-lowering effect of bempedoic acid (15). Similarly, data from a recent oral PCSK9 inhibitor trial showed only a marginal additive effect in the bempedoic acid-treated comparator group when added to stable statin therapy (18).

The results of HACOL-ACS will also provide meaningful information for patients beyond the German healthcare system. While the trial design is adapted to national settings, the proportion of patients achieving guideline-recommended LDL-C targets at the end of the trial with double and triple therapies will be applicable both in regions with sequential dose escalations and in those allowing triple therapy from the beginning.

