### Study design

The study design according to protocol version 3.0 dated 13 November 2023, is depicted in Figure 1. This is a single-center, open-label, prospective, interventional study designed to precisely estimate the proportion of patients who successfully achieve LDL-C treatment targets as recommended by current guidelines. In Stage I, up to 135 patients will treated for 6 weeks with atorvastatin (at least 40 mg/day or equivalent) plus ezetimibe (10 mg/day). The chosen statin and its dose reflect the recommended regional background medication, established by consensus among local PCI hospitals, the regional Association of Statutory Health Insurance Physicians, and regional representatives for outpatient cardiologists. This consensus balances additive LDL-C-lowering efficacy against potential side effects (7). Thereafter, in Stage II, patients are split into two groups:

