#### Study intervention/treatment

After the index hospitalization and enrolment into the trial, standard medication including atorvastatin (40 mg/day) and ezetimibe (10 mg/day) will be recommended. After 6 weeks (Stage I), a study visit will be conducted at the institution and another lipid test will be performed. Next (Stage II), study medication (bempedoic acid, 180 mg/day, provided by Daiichi Sankyo, Munich, Germany) will be given at V2 to patients with LDL-C 1.4-2.8 mmol/L (55-110 mg/dL) (Group A), and patients with LDL-C < 1.4 mmol/L (55 mg/dL) will be continued on the background medication with the previous dosing (Group B). Patients with LDL-C > 2.8 mmol/L (110 mg/dL) at week 6 will be directly referred for PCSK9 inhibition outside the trial. Patients with LDL-C ≤ 2.8 mmol/L (110 mg/dL) mg/dL will have a revisit (V3) after another 8 weeks, including another lipid test.

The dose of bempedoic acid— 180 mg/day—will not be modified. The background medication is atorvastatin (40 mg/day) plus ezetimibe (10 mg/day), which is the standard discharge medication. If—despite explanation about the study protocol—patients are escalated by their treating physicians to higher doses of atorvastatin (>40 mg/day) or switched to rosuvastatin (minimum 20 mg/day), this will be considered stable baseline medication with regard to the study protocol. Switching between medications and de-escalation of statin treatment are strongly discouraged. A sensitivity analysis excluding patients with escalated doses of atorvastatin or switching to equal doses of rosuvastatin is planned.

Remaining study medication will be counted upon return at V3. Aside from adherence to lipid-lowering therapy, no other restrictions apply to routine care.

This strategy reflects current guideline recommendations to either initiate or escalate to a dual lipid-lowering therapy with a high-dose potent statin in combination with ezetimibe prior to adding a third compound (17). It also supports the generalizability of HACOL-ACS results to broader patient populations.

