#### Follow-up

Treatment on-site visits will be performed at V2 (Week 6 ±5 days) and V3 (Week 14 ±5 days). An additional safety follow-up visit will be conducted by telephone at week 15 (±5 days). The assessments performed at each visit are summarized in Table 1. Adherence to background medication will be assessed by interview, and adherence to bempedoic acid will be assessed by pill count.

**Table 1 T1:** Study calendar.

Visit	Screening	Baseline	Treatment visits		Safety follow-up visit (by phone)
		V1	V2	V3^a^	V4^b^
Time	1–14 days prior to baseline	Day 0	Week 6 (±5 days)	Week 14 (±5 days)	Week 15 (±5 days)
Informed consent	x				
Inclusion/exclusion criteria	x				
Demographic data	x				
Medical history	x				
Physical examination/vital signs		x	x	x	
Quality of life questionnaire (SF-36)		x	x	x	
Lipid profile (including total cholesterol, HDL-C, LDL-C, and triglycerides)	x^c^		x	x	
Uric acid, creatine kinase	x^c^		x	x	
Dispense of study medication			X^d^		
Liver function test			x	x	
Serum *β*-hCG pregnancy test (patients of childbearing potential)	x		x	x	
Concomitant medication	x	x	x	x	
Adverse events				x^e^	x^e^
Return of IMP				x	

AEs, adverse events.

a Patients with LDL-C ≤ 2.8 mmol/L (110 mg/dL) will have a revisit (V3) 8 weeks after V2.

b Telephone inquiry regarding AEs after IMP discontinuation (triple therapy group) and equivalent time point for dual therapy group.

c Admission laboratory values from routine testing may be included within the screening period.

d Study medication will be given to patients with LDL-C ≥ 1.4 mmol/L (55 mg/dL). Patients with LDL-C > 2.8 mmol/L (110 mg/dL) will be directly recommended for PCSK9 inhibition.

e Triple therapy group and double therapy group from dispensation of IMP onward (V2).

All trial data will be entered into an Electronic Case Report Form provided by the Center for Clinical Trials, which will also conduct the monitoring.

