## Statistical analysis

All analyses will be descriptive and performed in the ITT population. Demographic and baseline measurements will be summarized using descriptive methods. In the primary analysis, the proportion of responders and an exact descriptive 95% Clopper–Pearson confidence interval (CI) will be calculated. Patients with missing values for the primary endpoint will be counted as treatment failures in the ITT analysis, that is, as patients who did not achieve LDL-C guideline targets of <1.4 mmol/L (55 mg/dL) after treatment for 14 weeks.

Explanatory analyses for secondary endpoints will be carried out separately for Groups A and B. Responder rates will be examined using the exact 95% Clopper–Pearson CIs, and continuous data will be compared exploratorily using two-sided paired *t*-tests, with a two-sided level significance of 5%. In addition, mean changes in continuous laboratory parameters will be compared between Groups A and B using an analysis of covariance model, including baseline values at the start of the study and group assignment.

For the primary endpoint, a subgroup analysis will be carried out. Patients in the triple therapy group who fail to achieve the LDL-C guideline target of LDL-C < 1.4 mmol/L (55 mg/dL) after Stage I will be divided into four subgroups depending on their LDL-C level:
Group: LDL-C of 55 – ≤ 68.75 mg/dL (1.4–≤1.8 mmol/L).Group: LDL-C of 68.75 – ≤ 82.5 mg/dL (1.8–≤2.1 mmol/L).Group: LDL-C of 82.5 – ≤ 96.25 mg/dL (2.1–≤2.5 mmol/L).Group: LDL-C of 96.25 – ≤ 110 mg/dL (2.5–≤2.8 mmol/L).In every subgroup, the proportion of responders will be examined and exact 95% Clopper–Pearson CIs will be calculated. To evaluate the robustness of the results, efficacy analyses will be repeated in the PP population (sensitivity analyses).

Descriptive analyses will be performed to assess adverse events and serious adverse events. As this is an exploratory study, no adjustment for multiplicity will be performed. Confidence intervals and respective *p*-value will only be assessed descriptively.

Access to the final trial dataset will be centralized at the Center for Clinical Trials.

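### Group A is described both with and without an upper LDL-C limit, and patients referred directly to PCSK9 inhibition at week 6 have no fixed place in the overall rate or the PCSK9-need count

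*Protocol article*

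**What the plan says.** **Two-way split without an upper limit.** Study design states "Thereafter, in Stage II, patients are split into two groups". The text below Figure 1 continues: "Group A will consist of the subgroup of patients who do not reach the LDL-C guideline target". The same sentence adds that this group receives bempedoic acid for 8 weeks. The Methods part of the abstract also escalates everyone who misses the target at week 6.

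**Restricted Group A and a third route.** Study intervention/treatment gives the study drug to "patients with LDL-C 1.4-2.8 mmol/L (55-110 mg/dL) (Group A"). It then states "Patients with LDL-C > 2.8 mmol/L (110 mg/dL) at week 6 will be directly referred for PCSK9 inhibition outside the trial". V3 is planned only for patients at or below 2.8 mmol/L, which Table 1 footnote a repeats. Footnote d begins "Study medication will be given to patients with LDL-C ≥ 1.4 mmol/L (55 mg/dL") with no ceiling, and its next sentence sends patients above 2.8 mmol/L to PCSK9 inhibition.

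**Analysis.** The primary endpoint is a proportion in Group A (Study endpoints). Statistical analysis uses the ITT population and adds "Patients with missing values for the primary endpoint will be counted as treatment failures in the ITT analysis". Secondary endpoints are analysed by Group A and Group B. The four subgroup bands for the primary endpoint end at 110 mg/dL.

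**Questions to be answered.** The abstract promises a responder rate in the whole study population. The third question in Background asks "how many patients miss the target despite escalated oral triple lipid-lowering therapy and therefore need referral for PCSK9 inhibition", and that section also promises to quantify the need left unmet by stepwise oral therapy.

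**The concern.** The main result is a single proportion with a confidence interval, so its denominator should be readable in one way only. A patient above 2.8 mmol/L at week 6 has missed the target, which fits the Group A sentence below Figure 1. That patient receives no bempedoic acid and has no V3, so the week-14 value is missing. An analyst working from that sentence and the missing-value rule could record a failure of triple therapy for someone who never started it.

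On the restricted definition the problem moves. The direct referral is then in neither group, although Study design provides for only two. The missing-value rule is written for the primary endpoint alone and secondary analyses run by group, so nothing fixes how this patient enters the overall week-14 rate. The third question counts only misses after triple therapy, so patients whom the plan itself sends to PCSK9 inhibition at week 6 are outside it. Answered literally, it understates how many patients oral therapy leaves short of target, and the error favours the strategy.

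**Working it through.** **1. The plan's own figure.** Sample size asks for an exact two-sided 95% Clopper–Pearson interval of width 26.4% at a responder rate of 0.5 with n = 60. For 30/60 the interval is 36.8% to 63.2%, width 26.39%. The figure reproduces. The total of 2 × 60 + 15 = 135 doubles 60 because about half of those enrolled are expected to miss the target, which again leaves no separate share for direct referrals.

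**2. Which reading of Group A do the passages support?**
- No upper limit: the abstract, the two-group split in Study design, and the first clause of the Group A sentence.
- 1.4–2.8 mmol/L: the second clause of that sentence (the group receives bempedoic acid), Study intervention/treatment, Table 1 footnote a, the second sentence of footnote d, and the subgroup bands ending at 110 mg/dL.

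The second list is more specific and consistent, so the primary denominator can be inferred as patients allocated to bempedoic acid at V2.

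**3. What the less natural reading would do.** Let k be the number of direct referrals. The documents give no value, so k is an assumed range. With 30 responders among 60 treated, the primary rate is 30/60 = 50.0%. If direct referrals were added as failures it would be 30/(60 + k):
- k = 3: 30/63 = 47.6%
- k = 15: 30/75 = 40.0%

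**4. Overall week-14 rate and PCSK9 need.** Assumptions: 60 patients in Group B, all still at target at week 14; 30/60 responders in Group A; no other losses.
- Without direct referrals: overall rate (60 + 30)/120 = 75.0%; PCSK9 need 30/120 = 25.0%.
- With them: overall rate 90/(120 + k); PCSK9 need (30 + k)/(120 + k).

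| k | Overall rate | PCSK9 need |
|---|---|---|
| 0 | 90/120 = 75.0% | 30/120 = 25.0% |
| 3 | 90/123 = 73.2% | 33/123 = 26.8% |
| 6 | 90/126 = 71.4% | 36/126 = 28.6% |
| 10 | 90/130 = 69.2% | 40/130 = 30.8% |
| 15 | 90/135 = 66.7% | 45/135 = 33.3% |

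The last row reaches the maximum enrolment of 135.

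**The case against.** The strongest reply is that the primary denominator is not really open. The Group A sentence carries a second condition, receipt of bempedoic acid, which direct referrals do not meet, and every detailed passage agrees with 1.4–2.8 mmol/L. Figure 1 is not shown and may display the third route. This reply stands. A reader might infer that the primary result could be anything from 50.0% down to 40.0%, depending on the definition chosen. The documents do not support that, because the lower values need a reading that the detailed passages contradict.

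A reader might also infer that the plan removes direct referrals from the overall rate. No passage says so. A rate in the whole population, analysed by ITT, is compatible with counting them as not at target. Denominator detail for a secondary endpoint may also be in the full protocol or in an analysis plan that is not shown, and silence on it would not by itself be an error.

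Finally, PCSK9 need is a Background question and not a listed endpoint, and these patients have a V2 value, so they can be counted. That is also true. It shows that the gap is easy to close. It does not alter the wording of the third question, which is limited to patients on triple therapy, or the promise in the same section to quantify the remaining need.

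**Conclusion.** The point holds as an inconsistency to reconcile and a counting rule to fix. The article describes a two-way split with no ceiling in some places and a bounded Group A with a third route in others. The intended primary denominator can be inferred, so the primary estimate is at risk only if the missing-value rule is applied to direct referrals. The practical consequence lies with the overall week-14 rate, where their handling is undefined, and with the PCSK9-need figure, which would be understated if the third question is answered as worded.

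For an assumed 3 to 15 direct referrals, the difference is 1.8 to 8.3 percentage points in each figure (75.0% against 73.2%–66.7%; 25.0% against 26.8%–33.3%). These sizes rest on the assumed k, on all of Group B staying at target, and on half of Group A responding. They are illustrations and not forecasts.

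**What to change.** - Reconcile the abstract, Study design, the Group A sentence below Figure 1, Study intervention/treatment and Table 1 footnote d on who forms Group A and on the existence of a third route.
- Name the primary denominator as patients allocated to bempedoic acid at V2, and apply missing-equals-failure within that set only.
- Report direct referrals at V2 as a third group with its own count.
- Count that group as not at target in the overall week-14 proportion.
- Report PCSK9 need as (direct referrals at V2 + Group A not at target at V3) / all enrolled.

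The cost is some wording and a few table rows. No new data are needed, because LDL-C is measured at V2. The overall success rate becomes slightly lower. Trial status gives recruitment dates up to March 2026, so the wording should be settled before the analysis is run. No position is taken on the referral threshold or on who should receive which treatment.

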### Study population and inclusion

The study population will comprise up to 135 patients aged ≥18 and ≤85 years following acute percutaneous coronary intervention for STEMI or non-STEMI (NSTEMI), all on high-intensity oral lipid-lowering therapy. Importantly, baseline parameters will be used to demonstrate that patients enrolled in the HACOL-ACS trial are representative of a real-world cohort described previously at our institution, which showed mean LDL-C levels of 3.9 ± 0.7 mmol/L (149 ± 27 mg/dL) (7).

Inclusion criteria for the trial are as follows: patients of all sexes aged between 18 and 85 years, who have provided written informed consent, had NSTEMI or STEMI with successful coronary intervention within 7 days prior to screening, have a therapy-naïve LDL-C > 2.6 mmol/L (100 mg/dL), and are able to cooperate with the protocol regimen and follow-up.

Exclusion criteria are as follows: history of gout, scheduled surgery within the next 4 months, inability to attend study site revisits, participation in another clinical trial within 30 days prior to study start or during the trial, known hypersensitivity to any of the components of the medications used, pregnancy or breastfeeding, severe renal disorders (defined as estimated glomerular filtration rate <30 mL/min/1.73 m^2^) or requiring dialysis for end-stage renal disease, history of tendon disorders or tendon rupture, or requirement for placement in a mental institution by court or official order.

#### Study intervention/treatment

After the index hospitalization and enrolment into the trial, standard medication including atorvastatin (40 mg/day) and ezetimibe (10 mg/day) will be recommended. After 6 weeks (Stage I), a study visit will be conducted at the institution and another lipid test will be performed. Next (Stage II), study medication (bempedoic acid, 180 mg/day, provided by Daiichi Sankyo, Munich, Germany) will be given at V2 to patients with LDL-C 1.4-2.8 mmol/L (55-110 mg/dL) (Group A), and patients with LDL-C < 1.4 mmol/L (55 mg/dL) will be continued on the background medication with the previous dosing (Group B). Patients with LDL-C > 2.8 mmol/L (110 mg/dL) at week 6 will be directly referred for PCSK9 inhibition outside the trial. Patients with LDL-C ≤ 2.8 mmol/L (110 mg/dL) mg/dL will have a revisit (V3) after another 8 weeks, including another lipid test.

The dose of bempedoic acid— 180 mg/day—will not be modified. The background medication is atorvastatin (40 mg/day) plus ezetimibe (10 mg/day), which is the standard discharge medication. If—despite explanation about the study protocol—patients are escalated by their treating physicians to higher doses of atorvastatin (>40 mg/day) or switched to rosuvastatin (minimum 20 mg/day), this will be considered stable baseline medication with regard to the study protocol. Switching between medications and de-escalation of statin treatment are strongly discouraged. A sensitivity analysis excluding patients with escalated doses of atorvastatin or switching to equal doses of rosuvastatin is planned.

Remaining study medication will be counted upon return at V3. Aside from adherence to lipid-lowering therapy, no other restrictions apply to routine care.

This strategy reflects current guideline recommendations to either initiate or escalate to a dual lipid-lowering therapy with a high-dose potent statin in combination with ezetimibe prior to adding a third compound (17). It also supports the generalizability of HACOL-ACS results to broader patient populations.

#### Study endpoints

The primary endpoint is defined as the proportion of patients (%) in Group A who successfully achieve the European Society of Cardiology (ESC) LDL-C guideline target after Stage II. Secondary endpoints comprise the following: proportion of patients (%) who successfully achieve ESC LDL-C guideline targets [LDL-C < 1.4 mmol/L (55 mg/dL)] after treatment with dual therapy including atorvastatin (at least 40 mg/day or equivalent) plus ezetimibe (10 mg/day) at 6 and at 14 weeks; the proportion of patients (%) who successfully achieve the ESC LDL-C guideline targets after 14 weeks of treatment; the proportion of patients (%) who achieve American heart Association (AHA)/American College of Cardiology (ACC) guideline-recommended treatment targets of LDL-C < 1.8 mmol/L (70 mg/dL) after 14 weeks of treatment in the triple therapy group; mean change from baseline to week 6 and week 14 in LDL-C, total cholesterol, HDL-C, triglycerides, uric acid, creatine kinase, systolic and diastolic blood pressure, and heart rate; the proportion of non-compliant patients (%) taking less than 90% of the allocated study medication; and mean change from baseline to week 6 and to week 14 in quality of life.

Safety will be assessed by monitoring and recording all adverse events, serious adverse events, and certain laboratory parameters (further described under pharmacovigilance).

The primary endpoint was chosen to focus on the efficacy of the investigational compound in order to prevent that a higher than anticipated achievement rate of the LDL-C target on the baseline medication might result in an escalation subgroup being too small to conduct proper statistical analyses.

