## Pharmacovigilance

Adverse events will be recorded for all participants from the first application of bempedoic acid (or the equivalent time point for the double therapy group) until the last study visit. The safety of add-on treatment with bempedoic acid on top of atorvastatin and ezetimibe background therapy will be assessed by descriptive comparison of (serious) adverse events between the two treatment arms. This safety assessment (as detailed in Table 1) includes but is not restricted to the repetitive measurement of uric acid and creatine kinase as well as the assessment for tendon-related or other muscle-associated potential side effects.

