## Limitations

The study has a single-center, open-label, non-randomized design, which introduces potential bias. For example, the single-arm design inherits the risk that changes in food intake, general lifestyle, and background medication over time may influence LDL-C and, thereby, the estimate of LDL-C-lowering effects of bempedoic acid. Hence, our study is exploratory regarding the escalation strategy and non-comparative.

HACOL-ACS is a short-term feasibility trial testing the applicability of sequential add-on bempedoic acid when guideline-recommended LDL-C targets are not achieved with tolerated high-intensity statin treatment combined with ezetimibe. The purpose of the trial is to describe the extent of additive LDL-C lowering provided by the sequential escalation. Given the small sample size and short duration, the trial does not assess long-term outcomes and, therefore, relies on surrogate endpoints, limiting clinical inference.

The single-center design and the fact that the study will be conducted within a specific healthcare system with defined prescribing constraints will impact but not prevent external validity and applicability to other settings. However, these prescribing constraints would have similar applicability even in a multicenter trial in a single country. The constraints on lipid-lowering therapy, however, allowed for prescription of atorvastatin, rosuvastatin, and ezetimibe, which will allow to use the most potent statins.

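### No specified continuous endpoint starts at V2, so the added LDL-C lowering by bempedoic acid is not isolated, and week-14 creatine kinase change cannot stand alone as add-on safety

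*Protocol article*

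**What the plan says.** All references are to the Protocol article.

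- **Endpoints.** Study endpoints lists "mean change from baseline to week 6 and week 14 in LDL-C, total cholesterol, HDL-C, triglycerides, uric acid, creatine kinase", together with blood pressure and heart rate, and separately "mean change from baseline to week 6 and to week 14 in quality of life". No change from week 6 to week 14 is listed.
- **Start of the study drug.** Under Study intervention/treatment, bempedoic acid is dispensed at V2 (week 6), to Group A only. Stage I before it is newly started statin plus ezetimibe.
- **Source of the laboratory baseline.** Patients must have "had NSTEMI or STEMI with successful coronary intervention within 7 days prior to screening". Table 1 schedules lipids, uric acid and CK at screening, V2 and V3 but not at V1, and footnote c adds: "Admission laboratory values from routine testing may be included within the screening period". Vital signs and the SF-36 are taken at V1.
- **Analysis.** Statistical analysis plans paired t-tests without naming the visits. It also plans an ANCOVA comparing Groups A and B on mean change, with the study-start value and group as the only terms.
- **Purpose.** Limitations says the trial is to "describe the extent of additive LDL-C lowering provided by the sequential escalation". Background undertakes to show, patient by patient, what bempedoic acid adds to dual therapy. Pharmacovigilance assesses the safety of the add-on, including "repetitive measurement of uric acid and creatine kinase".

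**The concern.** The reference point is stated, not left open, and it lies six weeks before the drug under study. A baseline-to-week-14 change in Group A combines the response to statin plus ezetimibe with the response to bempedoic acid, and the first is expected to be much the larger. A report that follows the endpoint list would show a large fall in LDL-C with an interval around it. It would show no interval for the part that the trial is meant to describe.

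For CK the starting value is taken around an infarct, which itself raises CK. A fall from that value to week 14 is expected whatever happens after V2.

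The group comparison has a related problem. Group A consists of the patients who responded less well in Stage I. A week-14 LDL-C comparison adjusted only for study-start LDL-C carries that selection with it.

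**Working it through.** **Plan's own figure.** The continuous endpoints have no sample size of their own. The planned 60 triple-therapy patients reproduce: the exact Clopper–Pearson interval at 30/60 is 36.81% to 63.19%, width 26.4%. I use n = 60 below.

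**1. How much of the week-14 LDL-C change is the add-on step.** Inputs: 149 mg/dL (reference cohort, Study population and inclusion) and a 17% further reduction (Background). The Group A mean at V2 is assumed. Stage I = V2 − 149; Stage II = −0.17 × V2; share = Stage II / total.

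| V2 mean (assumed) | Stage I | Stage II | Total to week 14 | Share |
|---|---|---|---|---|
| 60 | −89 | −10.2 | −99.2 | 10% |
| 70 | −79 | −11.9 | −90.9 | 13% |
| 80 | −69 | −13.6 | −82.6 | 16% |
| 90 | −59 | −15.3 | −74.3 | 21% |

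If Group A starts above the cohort mean, the share is smaller still.

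**2. Precision at n = 60.** Half-width = 2.001 × SD of change / √60.
- From study start, SD = √(27² + s² − 2ρ·27·s). With assumed week-14 SD s of 12 to 15 and ρ of 0.2 to 0.6, the half-width is 5.6 to 7.3 mg/dL.
- From V2, SD = √(2s²(1 − ρ)). With assumed s of 12 to 15 and ρ of 0.5 to 0.9, the half-width is 1.4 to 3.9 mg/dL.

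The interval for the listed endpoint therefore cannot stand in for the missing one.

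**3. What a V2-to-V3 change would contain.** Group A is selected on V2 LDL-C. Assume V2 values are normal with mean 55 (about half miss the target, Sample size), SD 15 to 25, and visit-to-visit correlation ρ of 0.7 to 0.9. With no drug effect, the expected Group A change is −(1 − ρ) × (Group A V2 mean − 55).
- SD 15, ρ 0.9: −0.1 × (67.0 − 55) = −1.2 mg/dL.
- SD 25, ρ 0.7: −0.3 × (73.7 − 55) = −5.6 mg/dL.

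Group B drifts the other way, by about +1 to +6 mg/dL. The 17% effect over the same V2 means is about −11 to −13 mg/dL.

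**4. The A-versus-B ANCOVA on LDL-C change from study start.** With study-start LDL-C as covariate, the group coefficient is the same whether the outcome is the change or the week-14 value. If study-start LDL-C is uncorrelated with V2, the coefficient is the difference in week-14 means. With a true 17% effect:
- SD 15, ρ 0.7: A = 0.83 × (55 + 0.7 × 12.0) = 52.6; B = 55 − 0.7 × 12.0 = 46.6; A − B = +6.0.
- SD 25, ρ 0.9: A = 0.83 × (55 + 0.9 × 18.7) = 59.6; B = 55 − 0.9 × 19.9 = 37.1; A − B = +22.5.

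Simulating the model with study-start-to-V2 correlation from 0 to 0.5 gives +4 to +23 mg/dL in every case. Triple therapy looks worse than dual therapy although the drug works as assumed.

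**5. CK.** The documents give no CK values, so these are illustrative: study start 500 to 2000 U/L, V2 120, V3 240.
- Week-6 change: 120 − 500 = −380, to 120 − 2000 = −1880.
- Week-14 change: 240 − 500 = −260, to 240 − 2000 = −1760.
- V2 to V3: +120 in both cases.

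The week-14 figure alone is a large fall despite a doubling on treatment. The rise shows only when week 6 and week 14 are set side by side.

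**The case against.** A reader might infer that the add-on effect and any CK or uric acid signal are simply not measured. The documents do not support that.

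- Lipids, uric acid and CK are sampled at both V2 and V3, and Groups A and B are analysed separately. In the same patients, mean week-14 change minus mean week-6 change is the mean V2-to-V3 change. This stands: the point estimate can be derived. Its paired SD, interval and test cannot be derived from the two reported summaries.
- The paired t-tests name no visits, so V2 versus V3 is not excluded. This stands, but the endpoints they serve all run from study start.
- The primary endpoint is already anchored at V2. Group A is off target there by definition, and the subgroup analysis splits it by V2 LDL-C band. This stands for target attainment, not for the amount of lowering.
- For CK and uric acid, an infarct-related fall common to both groups drops out of the ANCOVA, so a rise confined to Group A could appear as a group difference. Adverse events are also recorded from V2. This stands, so it would be too strong to say that CK must look improved even if it rose. Footnote c permits an admission sample but does not require one.
- Acute-phase baselines are chiefly a laboratory matter. Vital signs and the SF-36 are taken at V1, 1 to 14 days after screening, and no stated aim needs the add-on effect on them.
- The analyses are declared exploratory and non-comparative. This limits the severity but does not reconcile the endpoint list with the stated purpose.

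**Conclusion.** The point holds in limited form and should be fixed before analysis. Every listed mean-change endpoint, and the ANCOVA covariate, refers to study start. The purpose given in Background and Limitations needs a change from V2. On the cited 149 mg/dL and 17%, with an assumed V2 mean of 60 to 90 mg/dL, only 10% to 21% of the listed LDL-C change is the add-on step. The A-versus-B LDL-C ANCOVA would favour Group B by about 4 to 23 mg/dL under the assumptions in the working. It should not be read as a bempedoic acid effect.

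For CK the conclusion is qualitative: the week-14 change cannot be read alone as add-on safety. Its size rests on assumed values.

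The primary endpoint, sample size and data collection are unaffected. A V2-to-V3 change would not be a pure drug effect either, since about 1 to 6 mg/dL of it in Group A may be regression to the mean.

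**What to change.** 1. Add as a secondary endpoint the Group A V2-to-V3 change with a 95% CI, in patients with both values: absolute and percent for LDL-C, absolute for uric acid and CK, with CK as a median or on the log scale.
2. Name V2 versus V3 in the paired t-tests for this endpoint.
3. Report Group B over the same interval descriptively only, since its drift runs opposite to that of Group A.
4. State that the V2-to-V3 LDL-C change includes regression to the mean, and give the size under stated assumptions.
5. State that the A-versus-B LDL-C ANCOVA on change from study start is not interpreted as a bempedoic acid effect, and that week-14 CK change is not read alone as add-on safety.
6. Keep baseline-to-week-6 change as the description of Stage I and baseline-to-week-14 change as that of the whole strategy. V2-referenced SF-36 and vital signs are optional.

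Cost: wording in the analysis plan and a few table columns, with no new data or patients. Trial status reports recruitment up to March 2026, so the addition should be dated and fixed before the analysis is run.
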